#### Pregnancy

Women of child-bearing potential will have a urine pregnancy test performed within 24 hours of the first administration of study drugs, monthly for the duration of therapy, and at 1 month following completion of therapy.

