#### Inclusion Criteria

- Age at least 18 years at the start of the lead-in period
- AST or ALT greater than 40 IU/L within one year of the start of the lead-in phase and at least once during the lead-in phase
- Successfully complete a 28-day lead-in phase. Successful completion of the lead-in phase will require the participant's BMI at the end of the lead-in period to be within +/- 10% of their BMI obtained at the initial lead-in visit, as well as adherence to the alcohol consumption guidelines.
- Have a liver biopsy performed within 18 days of completing the lead in phase demonstrating features consistent with NASH without cirrhosis; NAS score of at least 4.
- Negative urine pregnancy test (for women of childbearing potential) documented within the 24-hour period prior to the first dose of study medication. Females of childbearing

potential must be using two reliable forms of effective contraception during the study (while on study drug and during follow-up)

- Demonstrated fatty liver on an imaging modality, either ultrasound, CT, or MRI, within 1 year of the start of the lead-in phase
- Participant agrees to discontinue use of other antioxidants such as vitamin E, vitamin C, glutathione, alpha-tocopherol, or non-prescribed complementary alternative medications (including dietary supplements, megadose vitamins, herbal preparations, and special teas) from the start of the lead-in phase through completion of the follow-up phase. A multivitamin at standard doses will be allowed.
- Participant agrees to discontinue use of silymarin or other milk thistle preparations, other than study medication, from the start of the lead-in phase through completion of the follow-up phase

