### **3.4.4 Safety measurements**

#### Laboratory evaluations

Participants will undergo laboratory tests according to the time and event schedule to monitor for medication toxicities.

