### 4.3 Treatment Phase

#### Study visit procedures

Study visits will occur at weeks 2, 4, 8, 12, 16, 20, 24, 32, 40, and 48 while the subjects are in the treatment phase of the study. Phone calls will be made to the participants at weeks 6, 28, 36 and 44 to monitor safety, compliance with study medication, and concurrent medications. There is an acceptable window +/- 1 day for visits at week 2, and 4, and a window of +/- 3 days for all other visits.

On the evening prior to the clinic visit at Week 2, study coordinators will instruct subjects by phone call to withhold their morning dose until they come to the clinic. This clinic visit will be scheduled around a subject's silymarin dosing such that prior to the end of the clinic visit, coordinators will witness the subject's ingestion of their dose and will then have a blood sample drawn between 30 minutes to 1 hour after dosing for the estimation of silymarin steady-state peak and trough plasma concentrations.

The following procedures will be performed at the study visits:

|                                |                                                                                 |
|--------------------------------|---------------------------------------------------------------------------------|
| Interim Medical History        |                                                                                 |
| Symptom-directed Physical Exam | Vital signs and weight at each visit; physical exam every 3 months or as needed |
| Adverse Event Assessment       | Each visit                                                                      |

|                                            |                                                                                                                                                                          |
|--------------------------------------------|--------------------------------------------------------------------------------------------------------------------------------------------------------------------------|
| Concurrent Medication Assessment           | Each visit                                                                                                                                                               |

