| CBC/Differential                           | Each visit                                                                                                                                                               |
| Chemistry                                  | Each visit; ALT, AST, AlkPO4, total bilirubin, direct bilirubin, albumin, BUN, creatinine, glucose.
Week 12, 24, and 48 only: fasting triglycerides, glucose, insulin |
| Pregnancy Test                             | Urine, each visit                                                                                                                                                        |
| TSH                                        | Weeks 24 and 48                                                                                                                                                          |
| PTor INR                                   | Weeks 24 and 48                                                                                                                                                          |
| Silymarin level                            | Weeks 2, 4, 12, 16, 24, 32, 40, 48                                                                                                                                       |
| EKG                                        | Week 12                                                                                                                                                                  |
| Sample Storage                             | 20ml serum, 20ml whole blood, 10ml plasma, 24ml urine each visit from week 2 to week 24 and then week 48 (fasting at weeks 12, 24, and 48)                               |
| Pharmacokinetic Sample                     | Each visit according to assigned schedule or random sample                                                                                                               |
| Liver biopsy and CBC, ALT, AST, HOMAr      | Week 48 (or end of treatment)                                                                                                                                            |
| Adverse Event Assessment for Mental Health | Each visit                                                                                                                                                               |

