| Questionnaires                   | Week 4: SF-36, CLDQ, CES-D, ASE                                                                                                        |

**4.5 Unscheduled visits:** Participants who have changes in severity or initiation of new symptoms, or who need to have laboratory tests repeated, will be asked to return to the study site for unscheduled evaluations.

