Appendix 1 = SyNCH Phase I- Pharmacokinetic Summary & Tables  
Appendix 2 = Phase I Safety Summary Report  
Appendix 3 = IND  
Appendix 4 = Common Toxicity Criteria for Adverse Events (CTCAE) v3.0  
Appendix 5 = Time Event Table  
Appendix 6 = Guidelines for diet and exercise  
Appendix 7 = Pathology Scoring System

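### Section 3.4.4 requires monthly pregnancy tests on therapy, but the section 4.3 schedule spaces them 8 weeks apart after week 24 and provides none at weeks 28, 36 or 44

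*Protocol*

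**What the plan says.** The Pregnancy paragraph of Protocol section 3.4.4 requires a urine test in women of childbearing potential within 24 hours of the first dose, then "monthly for the duration of therapy, and at 1 month following completion of therapy".

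Section 4.3 gives the working schedule. For the clinic visits it states: "Study visits will occur at weeks 2, 4, 8, 12, 16, 20, 24, 32, 40, and 48". The Pregnancy Test row of the procedures table reads "Urine, each visit". Phone calls are made "at weeks 6, 28, 36 and 44 to monitor safety, compliance with study medication, and concurrent medications".

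Three other places bear on the point:

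- Section 3.4.4, Laboratory evaluations: "Participants will undergo laboratory tests according to the time and event schedule". The list of appendices has "Appendix 5 = Time Event Table", but the table itself is not in the document at hand.
- Section 3.3, Inclusion Criteria: women of childbearing potential "must be using two reliable forms of effective contraception during the study".
- Section 4.5 covers unscheduled visits, including for participants "who need to have laboratory tests repeated, will be asked to return to the study site for unscheduled evaluations".

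**The concern.** Two parts of the protocol govern the timing of the same safety test. They agree up to week 24, while visits are at most 4 weeks apart, and part company when visits move to every 8 weeks. A site that works from the section 4.3 table will fall short of section 3.4.4 without noticing.

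This looks like an oversight. The other two elements of the 3.4.4 rule are carried through: the pre-dose test appears in the entry criteria and the baseline procedures, and the test one month after therapy appears at follow-up week 4 in section 4.4. Only the on-treatment rule is lost, and only where the visits thin out.

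What is at stake is exposure in early pregnancy. A conception soon after a visit could go untested through about 8 weeks of continued dosing, where the safety section intends about 4. No efficacy result depends on it.

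**Working it through.** The protocol states no figure to reproduce, so the check sets the required test times against the scheduled ones.

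**Inputs**

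- Required frequency: monthly during therapy (section 3.4.4).
- Clinic visits carrying a urine test: weeks 2, 4, 8, 12, 16, 20, 24, 32, 40 and 48 (section 4.3).
- Phone calls: weeks 6, 28, 36 and 44 (section 4.3).
- Visit windows: ±1 day at weeks 2 and 4, ±3 days at all other visits (section 4.3).

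**Tests due against tests scheduled, monthly read as 4-weekly**

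- Due: weeks 4, 8, 12, …, 48, which is 48 / 4 = 12 tests.
- Of these, coinciding with a visit: weeks 4, 8, 12, 16, 20, 24, 32, 40 and 48, which is 9 tests.
- Not covered: 12 − 9 = 3 tests, at weeks 28, 36 and 44. These are exactly the later phone-call weeks.
- After week 24 alone: 6 due (28, 32, 36, 40, 44, 48) and 3 scheduled (32, 40, 48). The whole shortfall lies in this half of the 48-week schedule.

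**The same, monthly read as calendar months of 30.4 days**

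- Weeks 24 to 48 span 24 × 7 = 168 days.
- 168 / 30.4 = 5.5, so 5 tests are due and 3 are scheduled: a shortfall of 2.

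**Longest interval between scheduled tests**

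| Period | Planned gap | Longest gap within windows |
|---|---|---|
| Week 4 to week 24 | 28 days | 28 + 3 + 3 = 34 days |
| Week 24 to week 48 | 56 days | 56 + 3 + 3 = 62 days |

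The window also works the other way: an 8-week gap can be as short as 56 − 3 − 3 = 50 days. Even that exceeds a month on either reading.

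**After adding tests at weeks 28, 36 and 44**

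All 12 four-weekly points are covered and the planned gap after week 24 returns to 28 days. It would be at most 34 days if the calls are held to the same ±3 days; section 4.3 states that window for visits only, so this is an assumption.

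**The case against.** The strongest reply is that this is an omission and not a contradiction. The section 4.3 table lists what is done at clinic visits. It does not say that pregnancy tests happen only there, and it sets no interval. Section 3.4.4 sets the interval. A site that tests at every visit and also between visits after week 24 breaches neither section. That is correct. What remains is that the body text gives no occasion for the between-visit tests: the contacts that fall at the right weeks are calls whose stated purposes do not include one.

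Second, section 3.4.4 refers laboratory tests to the time and event schedule, and the heading of section 4.0 points to Appendix 5. That table could already show tests at weeks 28, 36 and 44. This cannot be checked, and it limits the finding to the body text. If Appendix 5 does include them, section 4.3 still needs correcting to agree with it.

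Third, the practical risk is limited. Two forms of contraception are required, women contemplating pregnancy are excluded, the calls ask about safety, and the document at hand identifies no reproductive hazard of silymarin. All of this lowers the risk, but the protocol asks for monthly testing in addition to contraception, and a call is not a test.

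Fourth, 62 days is the extreme of the windows and the three-test shortfall depends on the 4-weekly reading. Both are fair points. The planned gap is still 56 days, and the calendar-month reading still leaves two tests unscheduled.

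**Conclusion.** The concern holds for the body text of the protocol. From week 24 to week 48, half of the scheduled treatment period, the scheduled interval between pregnancy tests is twice what section 3.4.4 sets: 56 days planned against 28. The shortfall per woman who completes treatment is three tests on a 4-weekly reading of monthly, or two on a calendar-month reading. The conclusion rests on the two sections as written and leaves open what Appendix 5 shows. It is a correction to a safety procedure that should be made; it has no bearing on the efficacy analysis, the type I error or the sample size.

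**What to change.** Keep the monthly rule in section 3.4.4 and make the schedule meet it. In the Pregnancy Test row of the section 4.3 table, in the sentence on phone calls, and in Appendix 5 if it does not already say so, add for women of childbearing potential:

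- a urine pregnancy test at weeks 28, 36 and 44, using a home kit dispensed at the preceding visit (weeks 24, 32 and 40);
- the result recorded at the call;
- confirmation of any positive or unreadable result at an unscheduled visit under section 4.5.

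Local laboratory tests or brief extra visits would also comply; home kits are the lighter option because they use contacts that already exist. Rewording section 3.4.4 to match the visits would remove the inconsistency only by lengthening the safety interval to 8 weeks, and is not advised.

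The cost is three kits per woman, one case report form field per call and no added routine visit. The protocol does not give the number of women of childbearing potential. If they are 10% to 40% of the 120 subjects (an assumption), that is 12 to 48 women and 3 × 12 = 36 to 3 × 48 = 144 kits. The drawback is that home results are self-reported, and an occasional unscheduled visit will be needed to confirm one.

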### **3.5 Premature discontinuation**

Treatment may be discontinued prematurely for the following reasons:

1. Participant requests termination of the study medication
2. Participant is intolerant of the study medication despite predetermined dose reductions and side effect management strategies
3. Safety concerns at the discretion of the investigator. These concerns will be documented in the source documents

Participants who discontinue treatment prematurely for the above reasons will be encouraged to remain in the post-treatment follow-up period for an additional 12 weeks, unless they withdraw consent. For those discontinued prematurely, blood samples will be obtained as listed for the week 48 end-of-treatment visit.

Patients who drop out after 6 months of treatment will be asked to undergo the liver biopsy. Those who drop out after fewer than 6 months of treatment or fail to undergo the follow up liver biopsy will be asked to undergo laboratory studies according to the follow up protocol.

### **4.0 Study visits (Appendix 5)**

At each visit, patients will be advised to limit alcohol intake to no more than one drink or equivalent (>12 grams) per day and no more than 2 drinks on any one occasion, and to record alcohol intake into a diary. Diet modification is usually accompanied by a recommendation to exercise 30-45 minutes a day, 3-5 times a week. Patients will be counseled to avoid non-prescribed medicines or complementary alternative medicines, including milk thistle preparations. Patients will be instructed to complete a diary through the lead in and dosing periods. The diary used during the lead in period will help assess patient compliance to diet, exercise, and alcohol regimen. The diary used during the treatment period will help assess study medication dosing and alcohol use. Patients will be instructed to record adverse events and concomitant medications. This will be reviewed at all visits.

#### **4.1 Lead-In Phase**

The lead-in phase will be comprised of 2 visits, 28 days apart. Overweight and obesity are now defined by using Body Mass Index (BMI). BMI is defined as weight (in kilograms) divided by height squared (in square meters). Each patient will be counseled to achieve and maintain a target weight/BMI. A target of 10% of baseline weight is often used as an initial goal of weight loss according to the NHLBI-NIDDK. During each visit of the lead-in phase, patients will have blood drawn for liver tests, the BMI determined, and undergo dietary counseling by a member of the study staff. Patients will be counseled to follow a healthy diet and lifestyle as recommended by the U.S. Department of Health and Human Services and the U.S. Department of Agriculture. Dietary recommendations include a decrease in saturated fats as well as total fats to <30% of total calories and macronutrient distribution of 45 to 55% carbohydrate, 25 to 35% fat and 15 to 20% protein. Patients will be provided with dietary counseling to maintain glycemic control as well as to maintain a target weight/BMI that reflects no more than a +/- 10% change of body weight, as measured during the first lead-in visit. Guidelines for diet and exercise counseling are appended (Appendix 6).

#### **4.2 Lead-In Visits**

##### **Visit 1**

Subjects will give a complete medical history and, have a physical examination. Patients will be advised to limit alcohol intake to no more than one drink or equivalent (>12 grams) per day and no more than 2 drinks on any one day, and to record alcohol intake into a diary. Moderate levels of exercise will be recommended for 30-45 minutes per day, 3-5 times a week.

All patients will have blood drawn for liver enzymes, blood chemistries, and a complete blood count including platelet count. The BMI will be determined, and they will undergo dietary counseling in a 30-minute session by a registered dietitian. Each patient will be counseled to achieve and maintain a target weight/BMI that reflects no more than a +/- 10% change in BMI between the 2 lead-in visits. Dietary recommendations include a decrease in saturated fats as well as total fats to <30% of total calories and macronutrient distribution of 45 to 55% carbohydrate, 25 to 35% fat and 15 to 20% protein.

Subjects will be instructed to complete a diary to record alcohol consumption, concomitant medications, and adverse events. This will be reviewed at all visits.

##### **Visit 2 (Day 28)**

Subjects will return for the final lead-in visit to evaluate whether they can proceed to the treatment period. At this visit, a physical examination (including weight and vital signs), BMI and any changes in medical history as compared to the first lead-in visit will be recorded. Blood tests will be done for complete blood count including platelet count, chemistry, liver enzymes, and a routine urinalysis. Blood will be collected for future studies. Patients with at least one liver enzyme greater than 40 IU/L (AST or ALT) will have a liver biopsy performed ideally within 14 days, but allowable up to 18 days, of completion of the lead-in phase. The liver biopsy results must be obtained prior to moving on to the treatment phase.

### **Repeat Lead-in Procedure**

Eligible patients must be randomized within 28 days of completion of the lead-in phase. Ideally, a liver biopsy will be performed within 14 days of completion of the lead in phase. The biopsy may be performed up to 18 days following the completion of the lead in phase, provided the patient still meets the +/- 10% change in BMI from the start of the lead-in phase and has adhered to the alcohol consumption guidelines, as determined at the time the biopsy is performed. If the biopsy is not performed within 18 days of completing the lead-in period, the 28 day lead-in period must be repeated. If the biopsy is performed within 18 days of completing of the lead-in period but the patient is not randomized within 28 days of completing the lead-in period, the patient may still be randomized up to 42 days following completion of the lead-in period. If the patient is randomized between 29 and 42 days after completing the lead-in period, the laboratory tests (liver enzymes, blood chemistries, and blood count) must be repeated, and the patient must still meet the +/- 10% change in BMI from the start of the lead-in phase and has adhered to the alcohol consumption guidelines.

## **4.2 Baseline/Randomization Procedures**

### *Liver biopsy*

Percutaneous liver biopsy will be performed within 28 days of randomization, during the 28-day period following completion of the lead in phase. The liver biopsy will be performed according to each sites' standard procedures; however, an adequate specimen of at least 1.5 cm in length is recommended. The biopsy core will be processed for histological analysis. The pathologist at each clinical site, or at the central pathology site as described below, will score the liver biopsy according to a grading scheme as described by Brunt et. al. and Promrat et.al., and as modified by the Nonalcoholic Steatohepatitis Clinical Research Network (NSCRN) recommendation. In the NSCRN grading scheme, five features were independently associated with the diagnosis of NASH: steatosis, ballooning, lobular inflammation, fibrosis, and absence of lipogranulomas. A NAS score of at least 4 detected by the local or central pathologist, as determined by each investigator, will be required for entry (Appendix 7).

Four slides from each patient's liver biopsy will be sent to a central pathology site at the Beth Israel Deaconess Medical Center, Boston, MA. The central pathology site will stain the slides (hematoxylin/eosin, trichrome) and the study pathologist will evaluate each biopsy at the end of the study without knowing which slides belong to which patients and assign a NAS. Pre- and post-treatment biopsy NAS will be determined for the primary efficacy analysis. Patients who meet all inclusion and no exclusion criteria at the end of the lead-in period and have liver biopsy findings consistent with NASH (NAS  $\geq$  4) will be randomized. A baseline (randomization) visit will take place within 28 days of successful completion of the lead-in period and following the liver biopsy. During this 28-day period, the inclusion and exclusion criteria will be verified. In addition, the following procedures will take place.

- A history and physical examination will be conducted
- Baseline laboratory studies including liver tests, complete blood count, serum electrolytes, BUN and creatinine, fasting glucose and insulin, and serum silymarin will be obtained
- Fasting serum and urine will be collected for storage and biomarker studies (oxidative stress, apoptosis, and fibrosis)
- Urinalysis
- HOMAr, determined by the formula:

$$\frac{\text{Glucose mg/dL} \times 0.05551 \times \text{Insulin mcUI/mL}}{22.5}$$

- Urine pregnancy test for women of childbearing potential
- Subjects will be advised on the following:
  - Maintain a diet and exercise program to support maintenance of weight with calorie requirements based upon usual food intake as determined by food intake diaries and diet histories
  - To maintain a lifestyle/ diet/ exercise program
  - Not to consume alcohol in excess of one drink (12 grams) per day and no more than 2 drinks on any one day
  - Not to consume any non-prescribed medicines, naturopathic remedies, or vitamins
- Contraceptive plans for women of childbearing potential
- Quality of life assessment (SF-36,), depression (CESD), symptom assessment (CLDQ), and Adherence Self Efficacy (ASE)
- Randomization, upon review of eligibility data

